#### **6.5.9. Surgery**

Caution is advised on theoretical grounds for any surgical procedures during the study. The appropriate interval of time between surgery and PF-07248144 required to minimize the risk of impaired wound healing and bleeding has not been determined.

Stopping PF-07248144 is recommended at least 5 days prior to surgery. [REDACTED]

[REDACTED]  
[REDACTED] Postoperatively, the decision to reinitiate PF-07248144 [REDACTED] treatment should be based on a clinical assessment of satisfactory wound healing and recovery from surgery.

#### **6.5.10. Rescue Medicine**

There is no rescue therapy to reverse the AEs observed with PF-07248144 [REDACTED]; standard medical supportive care must be provided to manage the AEs.

#### **6.6. Dose Modification**

Every effort should be made to administer PF-07248144 [REDACTED] on the planned dose and schedule. In the event of significant toxicity, dosing

may be interrupted and/or reduced as described below. In the event of multiple toxicities, dose modification should be based on the worst toxicity observed (and attribution for the combination). Participants are to be instructed to notify investigators at the first occurrence of any adverse symptom.

For fulvestrant, [REDACTED], dose modification should be made according to product labeling and in compliance with its local prescribing information.

### 6.6.1. Dosing Interruptions

In the event of significant toxicity, dosing may be interrupted as described in [Table 10](#) and [Table 11](#).

Doses omitted for toxicity are not replaced within the same cycle. The need for a dose reduction at the time of treatment resumption should be based on the criteria defined in [Table 10](#) and [Table 11](#), unless expressly agreed otherwise following discussion between the investigator and the sponsor.

Re-treatment following dose interruption for treatment-related toxicity may not occur until all of the following parameters have been met:

- Platelets count  $\geq 50,000/\text{mm}^3$ .
- Nonhematologic toxicities have returned to baseline or Grade  $\leq 1$  severity (or, at the investigator's discretion, Grade  $\leq 2$  if not considered a safety risk for the participant).

If treatment(s) interruption was due to worsening of hematologic or biochemical parameters, the frequency of relevant blood tests should be increased as clinically indicated.

If these conditions are met within 4 weeks of treatment(s) interruption, PF-07248144 [REDACTED] may be resumed. Refer to the Dose Reductions [Section 6.6.2](#) for adverse events requiring dose reduction at the time of treatment(s) resumption.

If participants require discontinuation of PF-07248144 [REDACTED] for more than 4 weeks at any time during the study, then study treatment should be permanently discontinued, unless the investigator's benefit/risk assessment suggests otherwise after discussion with the Sponsor's medical monitor.

In addition, for combination dose escalation and expansion, dose interruption of 1 or more investigational products may be considered depending on the type and severity of toxicity encountered and the likely attribution based on discussion and consensus of the investigator and Sponsor, see [Table 10](#) and [Table 11](#).

Please see [Appendix 13 \(Section 10.13\)](#) for management of participants who have active confirmed (positive by regulatory authority-approved test) or presumed (test pending/clinical suspicion) SARS-CoV2 infection.

Note: Cycles will not be extended to cover for the missed doses. Refer to [Section 6.1.1.1](#) for information on missed doses.

### 6.6.2. Dose Reductions

Following dosing interruption due to toxicity, the PF-07248144 [REDACTED], dose may need to be reduced when treatment is resumed. No specific dose adjustments are recommended for Grade 1 or 2 treatment-related toxicity.

Participants experiencing recurrent and intolerable treatment-related Grade 2 toxicity may resume dosing at the next lower dose level once recovery to Grade  $\leq 1$  or baseline is achieved.

Dose reduction of PF-07248144 [REDACTED] by 1 and, if needed, 2 dose levels will be allowed depending on the type and severity of toxicity encountered.

When a toxicity may be attributed to either PF-07248144 [REDACTED] and a dose reduction is needed, either the dose for PF-07248144 [REDACTED] may be reduced based upon the clinical investigator's assessment of the weight of contribution from each study treatment.

Participants requiring more than 2 dose reductions of the PF-07248144 [REDACTED] will be permanently discontinued from the treatment and enter the follow up phase, unless otherwise agreed between the investigator and the Sponsor. All dose modifications/adjustments must be clearly documented in the participant's source notes and CRF.

Once a dose has been reduced for a given participant, all subsequent cycles should be administered at that dose level, unless further dose reduction is required. Intra-participant dose re-escalation is not allowed unless agreed by both investigator and the sponsor.

Participants experiencing a DLT may resume dosing at the next lower dose level (if applicable) once adequate recovery is achieved, and in the opinion of the investigator and sponsor, the participant is benefiting from therapy.

The following tables provide guidance for dose modifications needed for nonhematologic- ([Table 10](#)) and hematologic- ([Table 11](#)) treatment related toxicities.

\_\_\_\_\_

\_\_\_\_\_

[REDACTED]

|            |            |
|------------|------------|
| [REDACTED] | [REDACTED] |
| [REDACTED] | [REDACTED] |
| [REDACTED] | [REDACTED] |
| [REDACTED] | [REDACTED] |
| [REDACTED] | [REDACTED] |

[REDACTED]

#### **6.7. Intervention After the End of the Study**

No intervention will be provided to study participants at the end of the study.

### **7. DISCONTINUATION OF STUDY INTERVENTION AND PARTICIPANT DISCONTINUATION/WITHDRAWAL**

#### **7.1. Discontinuation of Study Intervention**

In rare instances, it may be necessary for a participant to permanently discontinue study intervention (definitive discontinuation). Reasons for definitive discontinuation of study intervention may include the following:

- Objective disease progression;
- Global deterioration of health status requiring discontinuation;
- Unacceptable toxicity;
- Pregnancy;
- Significant protocol violation;
- Lost to follow-up;
- Participant refused further treatment;
- Study terminated by sponsor;

- Death;

Note that discontinuation of study intervention does not represent withdrawal from the study. If study intervention is definitively discontinued, the participant will remain in the study to be evaluated for safety follow-up and survival (Part 2 dose expansion). See the [SoA](#) for data to be collected at the time of discontinuation of study intervention and follow-up for any further evaluations that need to be completed.

In the event of discontinuation of study intervention, it must be documented on the appropriate CRF/in the medical records whether the participant is discontinuing further receipt of study intervention or also from study procedures, posttreatment study follow-up, and/or future collection of additional information.

See [Appendix 13 \(Section 10.13.3.4\)](#) for guidance for participants with active or presumed SARS-CoV2 infection.

### **ECG Changes**

A participant who meets the QTc criteria below based on the average of triplicate ECG readings will be discontinued from the study intervention.

- QTcF >500 msec.
- Change from baseline: QTcF >60 msec.

If a clinically significant finding is identified (including, but not limited to, changes from baseline in QTcF after enrollment), the investigator or qualified designee will determine if the participant can continue in the study and if any change in participant management is needed. This review of the ECG printed at the time of collection must be documented. Any new clinically relevant finding should be reported as an AE.

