### 8.2.3. Electrocardiograms

Standard 12-lead ECGs utilizing limb leads (with a 10-second rhythm strip) should be collected at times specified in the [SoA](#) section of this protocol using an ECG machine that automatically calculates the heart rate and measures PR, QT, and QTcF intervals and QRS

complex. Alternative lead placement methodology using torso leads (eg, Mason-Likar) is not recommended given the potential risk of discrepancies with ECGs acquired using standard limb lead placement. All scheduled ECGs should be performed after the participant has rested quietly for at least 10 minutes in a supine position.

At each time point (see the [SoA](#)), 3 consecutive ECGs will be performed at approximately 2 minutes apart to determine the mean QTcF interval.

To ensure safety of the participants, a qualified individual at the investigator site will make comparisons to baseline measurements. Additional ECG monitoring will occur if a) the mean value from the triplicate measurements for any postdose QTcF interval is increased by  $\geq 60$  msec from the baseline **and** is  $> 450$  msec; or b) an absolute QTcF value is  $\geq 500$  msec for any scheduled ECG. If either of these conditions occurs, then a single ECG measurement must be repeated at least hourly until QTcF values from 2 successive ECGs fall below the threshold value that triggered the repeat measurement. In addition, if verified QTcF values continue to exceed the criteria above, immediate correction for reversible causes including electrolyte abnormalities, hypoxia and concomitant medications for drugs with the potential to prolong the QTcF interval should be performed.

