If the QTcF interval reverts to less than the threshold criteria listed above, and in the judgment of the investigator(s) and sponsor, it is determined that the cause(s) of QTcF prolongation is something other than study intervention, treatment may be continued with regular ECG monitoring. If in that timeframe the QTcF intervals rise above the threshold values, the study intervention will be held until the QTcF interval decreases to below the threshold values. Participants will then restart the study intervention at the next lowest dose level. If the QTcF interval has still not decreased to  $< 480$  msec after 2 weeks, or if at any time a participant has a QTcF interval  $> 515$  msec or becomes symptomatic, the participant will be removed from the study. Additional triplicate ECGs may be performed as clinically indicated.

In some cases, it may be appropriate to repeat abnormal ECGs to rule out improper lead placement as contributing to the ECG abnormality. It is important that leads be placed in the same positions each time in order to achieve precise ECG recordings. If a machine-read QTcF value is prolonged, as defined above, repeat measurements may not be necessary if a qualified medical provider's interpretation determines that the QTcF values are in the acceptable range.

If a participant experiences a cardiac or neurologic AE (specifically syncope, dizziness, seizures, or stroke), an ECG (triplicate) should be obtained at the time of the event.

ECG values of potential clinical concern are listed in [Appendix 7 \(Section 10.7\)](#).

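### For the same confirmed QTcF prolongation, Section 7.1 stops study drug while Section 8.2.3 allows continuation or restart, and no visible text says which governs

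*Protocol*

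**What the plan says.** Section 7.1, under ECG Changes, sets the rule on replicate means: "A participant who meets the QTc criteria below based on the average of triplicate ECG readings will be discontinued from the study intervention". It lists two criteria as separate bullets with no connector: QTcF above 500 msec, and "Change from baseline: QTcF >60 msec". Either one being enough is the natural reading. The section opens by describing permanent discontinuation, although the ECG sentence does not repeat that word. It also keeps people under observation: "If study intervention is definitively discontinued, the participant will remain in the study to be evaluated for safety follow-up and survival". After the criteria it adds that, for a clinically significant finding, "the investigator or qualified designee will determine if the participant can continue in the study and if any change in participant management is needed".

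Section 8.2.3 requires additional monitoring if "the mean value from the triplicate measurements for any postdose QTcF interval is increased by" 60 msec or more and QTcF is above 450 msec, or if an absolute QTcF on any scheduled ECG reaches 500 msec. In either event, "then a single ECG measurement must be repeated at least hourly until QTcF values from 2 successive ECGs fall below the threshold value" that set off the repeats, and reversible causes are corrected if the prolongation persists. If QTcF reverts, the sponsor and investigator judge the cause: where "it is determined that the cause(s) of QTcF prolongation is something other than study intervention, treatment may be continued with regular ECG monitoring". Should QTcF rise again in that period, drug is held until QTcF is below the threshold and then restarted one dose level lower. Removal applies above 515 msec, with symptoms, or if QTcF is not below 480 msec after 2 weeks.

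The ECG footnotes to Tables 2 and 3 (Schedule of Activities) add that a mean rise of at least 45 msec, or a mean above 500 msec, should be re-evaluated by a qualified individual for confirmation.

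**The concern.** Both sections are directive and neither cites the other. A site that confirms a prolonged triplicate mean finds an instruction to stop drug in one place and, in the other, a route back to dosing. This is a cardiac stopping rule in a first-in-human study with no data monitoring committee (Section 9.6), so the choice should not depend on which section is opened first.

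Two things are at stake: the participant's exposure after the event, and the descriptive summary of adverse events leading to premature withdrawal from treatment (Section 9.4.5.2). Section 8.2.3 also words its endpoint as removal from the study. That sits badly with 7.1, where stopping drug leaves the participant in follow-up, and overall survival is a Part 2 secondary endpoint.

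**Working it through.** The plan gives no figure to reproduce. The check sets the two rules side by side on a confirmed triplicate mean, for an asymptomatic participant.

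**Rules**
- 7.1: mean QTcF > 500, or rise > 60.
- 8.2.3 trigger: (mean rise ≥ 60 and QTcF > 450), or an absolute QTcF ≥ 500.
- 8.2.3 removal: QTcF > 515, or symptoms, or not < 480 after 2 weeks.

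**Where the criteria fall.** 500 − 60 = 440, so from baselines above 440 msec the > 500 criterion is met first. 450 − 60 = 390, so from baselines of 390 to below 440 msec the rise criterion is met first, at a QTcF above 450 and up to 500. Below 390 msec a rise above 60 can leave QTcF at or below 450. These cut points do not rely on the 470 msec limit in exclusion criterion 10, which is not absolute: criterion 11 lets participants with a cardiac rhythm device be considered above it.

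| Confirmed mean | Example | 7.1 | 8.2.3 |
|---|---|---|---|
| QTcF > 500 to 515 | baseline 450, mean 508; rise 508 − 450 = 58 | stop (absolute criterion) | continue if reverted and non-drug cause agreed, or restart one level lower after a hold; removal only if not < 480 after 2 weeks |
| rise > 60, QTcF > 450 to 500 | baseline 400, mean 465; rise 465 − 400 = 65 | stop (rise criterion) | same routes; 465 is already < 480 and < 515, so no removal criterion is met |
| rise > 60, QTcF ≤ 450 | baseline 380, mean 445; rise 445 − 380 = 65 | stop (rise criterion) | not triggered |

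The first two rows are conflicts: different dosing actions for the same ECG. The third is not, because only 7.1 gives an instruction, and the Schedule of Activities confirmation step still applies since 65 ≥ 45.

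**How far the rules overlap.** On triplicate means, the only values that trigger 8.2.3 without meeting 7.1 are QTcF of exactly 500, or a rise of exactly 60 with QTcF above 450. Off triplicate means, 8.2.3 has work of its own. Its 500 msec limb refers to an absolute value on any scheduled ECG, and its hourly repeats are single ECGs. Tracings of 510, 490 and 485 average 1485 / 3 = 495. With a rise of 60 or less, the 510 tracing can trigger 8.2.3 while the mean does not meet 7.1.

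**Does other text rank the two?**
- The discretion sentence in 7.1 covers clinically significant findings generally and does not waive the criteria just above it.
- Section 7.1.1 allows treatment at the same or one lower dose, but requires perceived benefit and sponsor discussion, which the 8.2.3 restart sentence does not. It mentions neither QTc nor 8.2.3.
- Sections 4.3.5 and 6.6.2 let a participant resume dosing after a DLT. The DLT window is Cycle 1 of dose escalation, so this does not reach Part 2 (about 90–120 participants) or later cycles.
- Section 6.6.1 gives general conditions for re-treatment after an interruption and sets no order between the QTc rules.
- Section 8 requires immediate sponsor discussion of safety issues, but does not say which rule the sponsor should apply.

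**The case against.** The best defence is that the sections form one sequence: the Schedule of Activities confirms a prolonged mean, 8.2.3 repeats ECGs, corrects causes and lets a qualified reader overrule the machine, and 7.1 then applies to what is left. Confirmation is a real step and the point is limited to confirmed means because of it. It does not account for the 8.2.3 sentence directing a restart one level lower.

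It can also be said that hold and reduce is the protocol's general scheme (6.6.1, 6.6.2), that 7.1.1 permits the outcomes 8.2.3 describes, and that 6.6.1 uses discontinuation for what is really an interruption. This shows that a temporary stop could have been intended in 7.1. The ECG rule nevertheless stands in a section introduced as permanent discontinuation, gives no restart condition, and belongs to a protocol that disallows waivers (Section 8).

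Table 10, on nonhematologic dose modification, is redacted and might contain a QTc row. That limits the claim to the visible text. The two printed rules would still need to agree with each other and with the table.

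A reader might also infer that the 8.2.3 hold, restart and 515 msec text is redundant and should be deleted. The 510 msec tracing with a mean of 495 shows otherwise, since deletion would leave such cases without a rule.

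**Conclusion.** The point holds in a limited form. For a confirmed triplicate-mean QTcF above 500 and up to 515 msec, or a confirmed mean rise above 60 msec with QTcF above 450 and up to 500 msec, 7.1 requires discontinuation while 8.2.3 lets an asymptomatic participant continue conditionally or restart lower. Above 515 msec both stop drug. This rests on reading the 7.1 bullets as alternatives. If both were required, a mean of 510 msec with a 65 msec rise would still receive two different instructions.

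The number affected is probably small. The documents give no frequency, but Section 2.2.4 does not list QTc prolongation among the Grade 3 or higher treatment-related events seen in more than one of 59 participants.

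Several stronger readings are not supported:
- The rise above 60 msec with QTcF at or below 450 msec is a trigger mismatch, not a third conflict.
- Sites would not be expected to resume dosing alone, given the sponsor discussion required by Section 8.
- DLT classification is not affected.
- The removal wording in 8.2.3 should not be taken to end follow-up. Section 7.1 says stopping drug is not study withdrawal, and the reasons listed in 7.2 for leaving the study include no ECG finding. It is loose wording.

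Even so, two different dosing instructions for one cardiac finding are more than a missing detail and should be corrected.

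**What to change.** - State in both sections that, once the Schedule of Activities re-evaluation confirms a triplicate mean meeting 7.1, discontinuation under 7.1 governs. Say whether 7.1.1 may be used as a sponsor-approved exception; the same sentence can cover resumption after a QTc DLT under 4.3.5 and 6.6.2.
- Keep the repeat-ECG, correction, hold and restart, and 515 msec text in 8.2.3. Limit hold and restart to values that do not meet 7.1 on a confirmed triplicate mean, for example a single tracing of 500 msec or more with a mean at or below 500 msec and a mean rise of no more than 60 msec.
- Align the rise trigger: use one inequality at 60 msec, and state whether the 450 msec floor applies in 7.1 as well as 8.2.3.
- Replace removal from the study in 8.2.3 with discontinuation of study intervention, so that follow-up plainly continues.
- Check that Table 10 agrees.

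The cost is wording in two sections, a cross-reference, one table check and a clarification letter to sites. No assessment is added and the sample size does not change.

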#### **7.1.1. Request to Continue Study Intervention**

If the investigator feels the participant is still deriving benefit from the study intervention, the investigator should discuss with the sponsor to elect treatment for the participant at the same dose or 1 dose lower until such benefit no longer exists.

### **7.2. Participant Discontinuation/Withdrawal From the Study**

A participant may withdraw from the study at any time at his/her own request. Reasons for discontinuation from the study may include:

- Completed study follow-up;
- Study terminated by sponsor;
- Lost to follow-up;
- Refused further follow-up;

- Death.

At the time of discontinuing from the study, if possible, an end of treatment visit should be conducted. See the [SoA](#) for assessments to be collected at the time of study discontinuation and post-treatment follow-up and for any further evaluations that need to be completed.

If a participant withdraws from the study, he/she may request destruction of any remaining samples taken and not tested, and the investigator must document any such requests in the site study records and notify the sponsor accordingly.

If the participant withdraws from the study and also withdraws consent (see Section 7.2.1) for disclosure of future information, no further evaluations should be performed and no additional data should be collected. The sponsor may retain and continue to use any data collected before such withdrawal of consent.

Lack of completion of all or any of the withdrawal/early termination procedures will not be viewed as protocol deviations so long as the participant's safety was preserved.

#### **7.2.1. Withdrawal of Consent**

Participants who request to discontinue receipt of study intervention will remain in the study and must continue to be followed for protocol-specified follow-up procedures. The only exception to this is when a participant specifically withdraws consent for any further contact with him or her or persons previously authorized by the participant to provide this information. Participants should notify the investigator in writing of the decision to withdraw consent from future follow-up, whenever possible. The withdrawal of consent should be explained in detail in the medical records by the investigator, as to whether the withdrawal is only from further receipt of study intervention or also from study procedures and/or posttreatment study follow-up, and entered on the appropriate CRF page. In the event that vital status (whether the participant is alive or dead) is being measured, publicly available information should be used to determine vital status only as appropriately directed in accordance with local law.

#### **7.3. Lost to Follow-up**

A participant will be considered lost to follow-up if he or she repeatedly fails to return for scheduled visits and is unable to be contacted by the study site.

The following actions must be taken if a participant fails to return to the clinic for/attend a required study visit:

- The site must attempt to contact the participant and reschedule the missed visit as soon as possible and counsel the participant on the importance of maintaining the assigned visit schedule and ascertain whether or not the participant wishes to and/or should continue in the study.
- Before a participant is deemed lost to follow-up, the investigator or designee must make every effort to regain contact with the participant (where possible, 3 telephone

calls and, if necessary, a certified letter to the participant's last known mailing address or local equivalent methods). These contact attempts should be documented in the participant's medical record.

- Should the participant continue to be unreachable, he/she will be considered to have withdrawn from the study.

